## **2.1 Research Question**

Does a sustained, nurse home visiting program, offered to vulnerable mothers in Australia from the antenatal period to child age 2 years, improve parent care and responsivity, and the home learning environment at child age 2 years?

## **2.2 Rationale for Current Study**

This study is crucial for generating Australian evidence of effective interventions to reduce the impact of social and environmental factors predisposing infants and children to ill health and reducing their life potential, an issue of timely and significant policy interest at a state and federal level. Critically, the rigour and scope of this trial will determine the impact of a comprehensive Australian SNHV program commencing antenatally in an at-risk population group. Despite the rhetoric regarding the benefit of SNHV, this will be the first trial in Australia to test its benefit and cost-benefit both at scale and within the context of a population health conceptual framework (i.e.

not within a child protection framework). As such, this trial is a best-practice implementation and effectiveness model for professional home visiting in Australia, with significant implications for the development of early childhood policy and strategy throughout Australia.

### **3. STUDY OBJECTIVES**

#### **3.1 Primary Objectives**

The overarching aim of the right@home trial is to improve children's development and early learning so that school readiness and subsequent academic performance is improved. Currently we are only funded to follow children to age 2 years. Our team's thorough review of the measures available at 2 years indicates that very few reliably predict children's development and learning at school-age. Instead, we argue that assessing the parent and environmental factors that underpin healthy development and learning will provide more measurable and hence meaningful outcomes for the study. Based on discussions making use of the ERG, the research team members' expertise and knowledge of this field, and three reviews of the literature (e.g. Appendices 3 and 30), the team have chosen primary outcomes that support the brain areas involved in early development and learning (areas thought to be particularly susceptible to the environmental factors associated with disadvantage) and parenting outcomes. Thus, the primary objectives of this study are to evaluate, at child age 2 years old, the impact of a SNHV program offered to vulnerable Australian mothers, on:

1. Parent care: the parent's ability to provide a consistent, regular and supportive environment for their child-promoting child regulation
  - 1.1 Nutrition: e.g. consistent meal times, nutritious food
  - 1.2 Sleep: bedtimes, settling and infant crying
  - 1.3 Safety: internal and external home safety
2. Parent responsiveness: the parent's ability to tune in to their child's needs and to respond appropriately; and
3. Home environment: building a strong home learning environment through structured developmental promotion activities focusing on language.

The measures for these outcomes are outlined in Sections 4 and 7.

#### **3.2 Secondary Objectives**

The secondary objectives of this study are to evaluate, across child age 6 weeks to 2 years, the impact of a SNHV program offered to vulnerable Australian mothers on:

1. Maternal: Pregnancy outcomes, Quality of Life, Mental health, Parent wellbeing, General Health, Parenting self-efficacy, and Health service use;
2. Child: General health and functioning;
3. Sibling: Mental health/behaviour; and
4. Nurse: Ability to effectively engage with parents and Use and knowledge of evidence-based clinical strategies.

## **4. STUDY DESIGN**

### **4.1 Type of Study**

This is a longitudinal, randomised controlled, multi-site evaluation of a sustained nurse home visiting program compared with usual care. The program will be offered to families from the antenatal period to the final follow-up assessment at child age 2 years. Researchers responsible for collecting the data, but not families or nurses, will be blinded to participating families' randomisation status.

A critical feature of the current trial is that it is designed based on strict program logic (see Figure 2 below), which is lacking in many of the previous home visiting randomised trials. A recent review by Segal et al (2012) of home visiting programs to reduce child maltreatment showed that programs based on strict program logic were much more likely to be effective than those that were not. As such, we are designing the trial to ensure any effects can be clearly traced back to the intervention offered. Specifically, the right@home intervention is based on the MECSH SNHV program, but is being enhanced to include evidence-based strategies on three focus modules which specifically target the three primary outcomes measured at age 2 years: parent care and responsivity, and a supportive home learning environment.

Figure 2: Program logic for the right@home trial

[figure not shown]

## 4.2 Study Design Diagram

Figure 3: Study Design Diagram

[figure not shown]

**Figure 4: Detailed Study Design Diagram for Recruitment**

[figure not shown]

### Number of Subjects

An anticipated n=800 pregnant vulnerable mothers (see Eligibility criteria, Section 6.2) will be enrolled into this study (n=400 per arm).

### 4.3 Expected Duration of Study

The expected duration of the study is 5 years. Recruitment will take place over 12 months (2013) and families will be offered the intervention and followed for 2.5 years (2014-16). Final analysis, publication and reporting will take place in 2016-17.

### 4.4 Primary and Secondary Outcome Measures

Primary and secondary outcome measures are listed in Table 2 below, and the schedule of these measures is presented in Section 7. A description of the baseline measures and their psychometric properties is attached in **Appendix 4**. Measures have been chosen for:

- Meeting the study's strict program logic, i.e. as direct measures of the three primary areas of intervention,
- Acceptability to women and the feasibility of collection relative to cost and time burdens, and
- Where possible, strong psychometric properties, having normative data available for population comparisons and previous use in international and/or Australian published research, particularly home visiting trials.

As there are three targeted areas of intervention, there are three **primary outcomes**: (1) Parent care, (2) Parent responsiveness, and (3) Supportive Home Environment.

**Table 2: Primary and Secondary Outcome Measures**

| Measure                                                           | Description                                                                                                                                                                   |
|-------------------------------------------------------------------|-------------------------------------------------------------------------------------------------------------------------------------------------------------------------------|
| Demographics                                                      | E.g. psychosocial and socioeconomic risk factors collected via self report                                                                                                    |
| Contact details                                                   | Family and alternate contact details                                                                                                                                          |
| PRIMARY OUTCOMES                                                  |                                                                                                                                                                               |
| 1. Parent care:                                                   |                                                                                                                                                                               |
| Nutrition : child height and weight, mealtime diary report | Child height and weight collected via direct observation; study-designed diary based on LSAC diary measuring types of food consumed in 24-hours, collected via parent report. |
| Safety : Home safety audit                                 | Observational safety check to identify household hazards, adapted from the Safe Place Project intervention.                                                                   |
| Sleep : Sleep problems                                     | Single parent report item drawn from LSAC: "How much of a problem is your child's sleep", responses "none", "mild", "moderate", and "large".                                  |

| Measure                                                                                                                  | Description                                                                                                                                                                                                                                   |
|--------------------------------------------------------------------------------------------------------------------------|-----------------------------------------------------------------------------------------------------------------------------------------------------------------------------------------------------------------------------------------------|
| 2. Parent responsivity:                                                                                                  |                                                                                                                                                                                                                                               |
| Parent responsivity subscale (observational) of the Home Observation for Measurement of the Environment Inventory (HOME) | Quality and quantity of stimulation and support available to a child in the home environment. Assessed through observation and interview with the primary caregiver (usually the mother) of the child in the family home.                     |
| 3. Home Environment:                                                                                                     |                                                                                                                                                                                                                                               |
| Confusion, Hubbub and Order scale (CHAOS):                                                                               | Parent report scale specially designed to be administered to parents for assessing chaos in the child's home. A measure of confusion and disorganisation.                                                                                     |
| HOME                                                                                                                     | See above (observational and parent report subscales)                                                                                                                                                                                         |
| MacArthur Communicative Development Inventory (MCDI)                                                                     | Standardised parent report questionnaire to assess children's receptive and expressive language.                                                                                                                                              |
| SECONDARY OUTCOMES                                                                                                |                                                                                                                                                                                                                                               |
| Maternal                                                                                                          |                                                                                                                                                                                                                                               |
| Pregnancy Outcomes                                                                                                       | E.g. self-reported length of breastfeeding, immunisations                                                                                                                                                                                     |
| Family Psychosocial Screening Instrument                                                                                 | Parent report scale that assesses domestic violence, parental substance abuse, and social support/capital.                                                                                                                                    |
| Assessment Quality of Life (AQoL-8)                                                                                      | Self-reported multi-attribute utility health-related quality of life instruments for use as utility instruments which measure quality of life.                                                                                                |
| Maternal mental health: Depression, Anxiety, Stress Scale (DASS-21)                                                      | Three self report scales designed to measure the negative emotional states of depression, anxiety and stress.                                                                                                                                 |
| Parenting Wellbeing Index (PWI)                                                                                          | Self report questions about life satisfaction with 8 specific life domains. The domains are theoretically embedded, as representing the first level deconstruction of the global question: 'How satisfied are you with your life as a whole?' |
| General Health Questionnaire (GHQ-S1)                                                                                    | Single self report item assessing overall health                                                                                                                                                                                              |
| Parenting self-efficacy                                                                                                  | Self report items drawn from the Millennium Cohort Study, assessing how the mother feels about her life so far, e.g. the extent to which she feels that she gets what she wants out of life, feels in control and can run her own life.       |
| Health service use                                                                                                       | Self report questions designed for the study in consultation with investigators [name] and [name] (right@home health economists)                                                                                                                 |
| Health literacy                                                                                                          | Study-designed self report items assessing mothers' knowledge, attitudes and beliefs about paediatric health                                                                                                                                  |
| Parenting styles                                                                                                         | Three self report subscales drawn from LSAC, assessing parenting warmth, hostile parenting and inconsistent/irritable parenting.                                                                                                              |

| Measure                                                                            | Description                                                                                                                                          |
|------------------------------------------------------------------------------------|------------------------------------------------------------------------------------------------------------------------------------------------------|
| Child                                                                       |                                                                                                                                                      |
| General functioning: Pediatric Quality of Life Inventory (Peds-QL) – Infant Scales | Parent report scale that assesses a child on 5 subscales (physical functioning, physical symptoms, and emotional, social and cognitive functioning). |
| General Health: GHQ-SF1                                                            | See above                                                                                                                                            |
| Sibling*                                                                    |                                                                                                                                                      |
| Mental health/behaviour: Strengths and Difficulties Questionnaire (SDQ)            | Parent report scale designed to measure psychological adjustment in children (collected for right@home siblings aged 3-6 years old only).            |
| Nurse**                                                                     |                                                                                                                                                      |
| Dose, fidelity and clinical knowledge/practice                                     | Study-designed participant report items assessing use and knowledge of evidence-based clinical strategies                                            |

\* The SDQ will be collected (where parents agree) for all siblings aged 3-6 years as 3 years is the earliest age that the SDQ can be administered, and it is unlikely that the right@home intervention will have secondary effects on school-age children.

\*\*The dose of the intervention delivered and nurse fidelity will be measured via data collected after each home visit a nurse conducts.

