| SNHV                                                | D                                                                                                                        |         |
| 2 year face-to-face assessment                      | I                                                                                                                        | I       |
| A                                                   | Screening survey for pregnant women in antenatal clinics                                                                 |         |
| B                                                   | Women who meet the eligibility criteria and are interested in the RCT are visited in their home to obtain formal consent |         |
| C                                                   | After obtaining formal consent, eligible women will complete a baseline questionnaire                                    |         |
| D                                                   | Sustained nurse home visiting intervention                                                                               |         |
| E                                                   | Study 6 week follow-up to assess pregnancy, health care access and health literacy                                       |         |
| F                                                   | Study 6 month follow-up to collect new contact details, health literacy and health service use data                      |         |
| G                                                   | Study 1 year follow-up to assess primary and secondary outcomes                                                          |         |
| H                                                   | Study 18 month follow-up to collect new contact details, health literacy and health service use data                     |         |
| I                                                   | Study 2 year follow-up to assess primary and secondary outcomes                                                          |         |

The schedule for collecting primary and secondary outcomes is presented in Table 4 below. These were previously described in Section 4.5. Additional details about these measures and their psychometric properties are provided in Appendix 4.

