**Table 4: Study measures collected at each time point**

| Study Measure                                                        | Time point |    |    |    |     |    |
|----------------------------------------------------------------------|------------|----|----|----|-----|----|
|                                                                      | Enrol      | 6w | 6m | 1y | 18m | 2y |
| Demographics                                                         | X          | X  | X  | X  | X   | X  |
| Contact details                                                      | X          | X  | X  | X  | X   | X  |
| PRIMARY OUTCOMES                                                     |            |    |    |    |     |    |
| Maternal                                                      |            |    |    |    |     |    |
| Parent care: Nutrition, Safety, Sleep                                |            |    |    | X  |     | X  |
| Parent responsivity                                                  |            |    |    | X  |     | X  |
| Home Environment:                                                    |            |    |    |    |     |    |
| Confusion, Hubbub and Order scale (CHAOS)                            | X          |    |    | X  |     | X  |
| Home Observation for Measurement of the Environment (HOME) subscales |            |    |    | X  |     | X  |
| MacArthur Communicative Development Inventory (MCDI)                 |            |    |    |    |     | X  |
| SECONDARY OUTCOMES                                                   |            |    |    |    |     |    |
| Maternal                                                      |            |    |    |    |     |    |
| Pregnancy Outcomes                                                   |            | X  |    |    |     |    |
| Social support                                                       | X          |    |    | X  |     | X  |
| Quality of Life                                                      | X          | X  |    | X  |     | X  |
| Maternal mental health                                               | X          | X  |    | X  |     | X  |
| Parenting Wellbeing                                                  | X          |    |    | X  |     | X  |
| General Health Questionnaire                                         | X          | X  | X  | X  | X   | X  |

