| Parenting self-efficacy                                              | X          |    |    | X  |     | X  |
| Health service use                                                   |            | X  | X  | X  | X   | X  |
| Health literacy                                                      |            |    | X  |    | X   |    |
| Parenting styles                                                     | X          |    |    | X  |     | X  |
| Child                                                         |            |    |    |    |     |    |
| Mental and general health                                            |            |    |    |    |     | X  |
| General Health                                                       |            | X  | X  | X  | X   | X  |
| Sibling                                                       |            |    |    |    |     |    |

| Study Measure                                           | Time point |    |    |    |     |    |
|---------------------------------------------------------|------------|----|----|----|-----|----|
|                                                         | Enrol      | 6w | 6m | 1y | 18m | 2y |
| Mental health/behaviour                                 | X          |    |    | X  |     | X  |
| Nurse                                            |            |    |    |    |     |    |
| Use and knowledge of evidence-based clinical strategies | X          | X  | X  | X  | X   | X  |
| MONITORING VARIABLES                                    |            |    |    |    |     |    |
| Maternal social capital/sensitive issues                | X          |    |    | X  |     | X  |
| Child birth data                                        |            | X  |    |    |     |    |
| Child growth data (e.g. height & weight)                |            | X  | X  | X  | X   | X  |
| Intervention dose and fidelity                          |            | X  | X  | X  | X   | X  |

Time points: w=week, m=month, y=year. Enrolment will occur within a fortnight of screening at the antenatal hospital clinic. Monitoring items are variables that may be used to describe the sample or to control for potential confounding and are not collected as demographics.

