### Objectives/hypotheses:

Primary: At child age 2 years, compared with the usual care group, intervention mothers will demonstrate:

1. Improved parent care, i.e. the parent's ability to provide a consistent, regular and supportive environment for their child;
2. Improved parent responsiveness, i.e. the parent's ability to tune in to their child's needs and to respond appropriately; and
3. A more supportive home environment, i.e. building a strong home learning environment through structured developmental promotion activities focusing on language.

Secondary: At child age 2 years, compared with the usual care group, intervention mothers will demonstrate:

1. Maternal: Improved pregnancy outcomes, Quality of Life, Maternal mental health, Parent wellbeing, General Health, Parenting self-efficacy, Health literacy, and more effective Health service use. The latter will depend on the service, e.g. preventative healthcare and

management vs. emergency department visits, and will be determined in partnership with the study health economists.

2. Child: Improved mental and general health, and language
3. Sibling: Improved mental health/behaviour
4. Nurse: Increased use and knowledge of evidence-based strategies

We have not powered the trial to consider subgroups but there will be some analyses which will need to be restricted to a subgroup of the trial, e.g. anything that refers to current parenting attitudes or behaviours (as not all women will already have children). These subgroup analyses will only be powered for larger effect sizes than the primary outcomes, and will be provided in a future ethics modification once the final outcome measures are decided. Another subgroup analyses which the team may consider (and, again, power will be limited) is testing whether the findings appear to be consistent by site/state.

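### Breastfeeding length is asked only at 6 weeks and so is cut off there, and the protocol sets the health-literacy test at 2 years, when it is not scheduled for collection

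*Protocol*

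**What the plan says.** Table 2 (section 4.4) lists Pregnancy Outcomes among the maternal secondary outcomes and describes its content only by example: "E.g. self-reported length of breastfeeding, immunisations". Table 4 (section 7) marks the row "Pregnancy Outcomes" at 6 weeks and at no other contact. No other row of Table 4 names breastfeeding or immunisation.

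The Table 4 row "Health literacy" is marked at 6 months and 18 months, and is blank at enrolment, 6 weeks, 1 year and 2 years. The key to Figure 5, in the same section, describes the first postnatal call differently: "Study 6 week follow-up to assess pregnancy, health care access and health literacy". Figure 5 also names health literacy at 6 and 18 months. It describes the 2-year visit only in general terms, as assessing primary and secondary outcomes.

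Section 10.3 opens the secondary hypotheses with "Secondary: At child age 2 years, compared with the usual care group, intervention mothers will demonstrate". The maternal list under that heading includes "Improved pregnancy outcomes, Quality of Life, Maternal mental health, Parent wellbeing, General Health, Parenting self-efficacy, Health literacy". Section 3.2 instead frames the secondary objectives over the period from 6 weeks to 2 years. It lists pregnancy outcomes but not health literacy, although the synopsis and Table 2 both include health literacy as a maternal secondary outcome.

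**The concern.** Length of breastfeeding is a duration. Asked once at 6 weeks, it is complete only for mothers who have already stopped. For the rest, the trial records that they were still feeding and nothing later under that item. Immunisations given after the call are likewise not scheduled for collection under any named item. These data would be lost at collection, so an analysis plan could not restore them.

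The item matters to this trial's rationale. Section 2 reports longer breastfeeding among overseas-born mothers as one of the benefits seen in the predecessor trial. Section 5.1.1 makes infant nutrition and immunisation part of the nurses' content.

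For health literacy the problem is one of agreement. The protocol fixes a test at an age for which its detailed schedule has no measurement, and its sections differ on when the outcome is collected and whether it is an objective.

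**Working it through.** There is no stated figure to reproduce. The check sets the passages side by side.

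| Source | Pregnancy outcomes | Health literacy |
|---|---|---|
| Section 3.2 | Listed; 6 weeks to 2 years | Not listed |
| Table 2 | Breastfeeding length and immunisations, as examples | Listed |
| Table 4 | 6 weeks only | 6 and 18 months only |
| Figure 5 | Named at 6 weeks only | Named at 6 weeks, 6 and 18 months |
| Section 10.3 | Hypothesis at 2 years | Hypothesis at 2 years |

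**Breastfeeding.** Write T for the age at stopping. A single report at 6 weeks gives min(T, 6 weeks) and an indicator of whether T is 6 weeks or less. That is enough for breastfeeding status at 6 weeks or duration truncated there. It does not give T for anyone still feeding.

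- Postnatal follow-up: 2 years × 52 = 104 weeks.
- Share covered by the single report: 6/104 = 0.058, about 6%.
- Share of mothers still feeding at 6 weeks: not in the document, so the number truncated cannot be stated.

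**Immunisation.** The 6-week report covers doses given by then. The protocol contains no immunisation schedule, so the amount missed cannot be calculated.

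**Health literacy.** Table 4 schedules two measurements. The last is at 18 months, 24 − 18 = 6 months before the age named in section 10.3. There is no scheduled 2-year value. With the 60% retention planned in section 10.1, 0.60 × 800 = 480 mothers are expected at the 2-year assessment, and this is the group to which the 2-year hypothesis would apply.

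**Room to repair.** Section 7 already plans calls at 6 and 18 months and home visits at 12 and 24 months, so later questions need no new contact.

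**The case against.** The strongest reply is that most of this is loose wording. The breastfeeding and immunisation entry is a list of examples, and no hypothesis in section 10.3 names either item. Health literacy is measured twice, and the randomised arms can be compared at 18 months. The 2-year phrase in section 10.3 is an umbrella over all the secondary outcomes. Placing health literacy in phone calls also fits section 10.1, which says the calls collect data partly to lighten the face-to-face assessments. Section 10.3 indicates that final outcome measures were still to be decided, so the follow-up questionnaires could yet carry the items.

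Much of this stands, and it rules out stronger readings that a reader might infer:

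- *That these secondary outcomes cannot be measured or tested.* This is true only of full breastfeeding length in mothers still feeding at 6 weeks. Health literacy is testable at 18 months.
- *That nothing about breastfeeding after 6 weeks could be seen.* The 24-hour food diary at 1 and 2 years might show current breastfeeding, and the health service questions, asked from 6 weeks to 2 years, might cover immunisation. The protocol says neither, so neither total loss nor coverage is established.
- *That a 2-year value is lost for all 800 women.* About 480 are expected to be assessed then.
- *That the predecessor trial supports the immunisation item too.* Section 2 reports no difference between groups there.

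What the reply does not answer is the schedule itself. The two examples are the only content given for the outcome, the first is explicitly a length, and Table 4 fixes one collection at 6 weeks. Figure 5's general description of the 2-year visit does not override a blank cell in the detailed table. Section 3.2's wider frame is a further disagreement with section 10.3.

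**Conclusion.** The point holds in a limited form. Followed as written, the protocol truncates breastfeeding length at 6 weeks for every mother still feeding, about 6% of the way through postnatal follow-up. It schedules no named collection of later immunisations. Neither loss can be sized from the document. Separately, section 10.3 sets pregnancy outcomes and health literacy at 2 years, while Table 4 last collects them at 6 weeks and 18 months respectively. Figure 5 and section 3.2 each disagree with Table 4 or section 10.3 in a further way.

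The conclusion assumes that Table 4 is the governing schedule and that no unlisted item covers breastfeeding or immunisation later. If the follow-up questionnaires do contain such items, the correction reduces to wording. Only secondary outcomes are involved; the primary outcomes, power and error rates are untouched. It is worth correcting because information on breastfeeding after 6 weeks that is not collected cannot be supplied by a later analysis plan.

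**What to change.** 1. Add a short item on whether and when breastfeeding stopped, and one on immunisation status, to later contacts already planned. The 6- and 18-month calls are the natural place; the 12- and 24-month visits are optional, given the stated wish to keep face-to-face assessments short. Mark the added contacts in Table 4.
2. If that is not wanted, relabel the outcome as breastfeeding status at 6 weeks, limit the immunisation item to doses given by then, and state the section 10.3 hypothesis at that age. This removes the contradiction but gives up breastfeeding length.
3. Restate the health-literacy hypothesis in section 10.3 at 18 months, the last scheduled measurement. This adds nothing to the 24-month visit.
4. Make Figure 5 agree with Table 4 on health literacy at 6 weeks. In section 3.2, list health literacy and align the time frame with the schedule.

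The cost is a few more questionnaire items per contact plus wording changes. Items added late would depend on longer recall, so the choice is best made before the 6-month calls begin.
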